**Statistical Methods:**

Statistical:

The primary summary measure, the CAARS-Inv:SV total ADHD symptom score as well as the Inattention subscale score, and Hyperactivity-Impulsivity subscale score, will be analyzed using a restricted maximum likelihood (REML)-based, mixed model repeated measures (MMRM) technique. The model will include the fixed, categorical effects of treatment, investigator, visit, and treatment-by-

visit interaction as well as the continuous, fixed covariates of baseline (last of scores at Visit 1 and Visit 2) score and baseline score-by-visit interaction. Secondary evidence of efficacy from the primary analysis will be based on the main effect of treatment and the treatment-by-visit interaction terms from the

MMRM analysis. This measure will be summarized separately during Study Period III. All statistical tests will be two-sided and will be conducted at the 5% significance level.

As supporting evidence, the CAARS-Inv:SV total ADHD symptom score as well as the Inattention subscale score, and Hyperactivity-Impulsivity subscale score, will be analyzed using a last observation carried forward (LOCF) analysis. Change from baseline to LOCF endpoint will be compared across treatments using an ANCOVA model with terms for baseline, treatment, and investigator.

The first gated secondary objective is to assess the efficacy of atomoxetine therapy compared with placebo on the total score of the Adult ADHD Quality of Life -29 (AAQOL-29) using a treatment contrast from the repeated measures mixed effects model at the final post baseline visit. The repeated measures model will include the same terms as that used for the primary efficacy measure. This measure will be summarized separately during Study Period III.

The next gated secondary objective is to assess the efficacy of atomoxetine therapy compared with placebo on the subscales of the AAQOL-29 in the following order: Relationship; Life Productivity; Psychological Health; and Life Outlook using a treatment contrast from the repeated measures mixed effects model at the final post baseline visit. The repeated measures model will include the same terms as that used for the primary efficacy measure. These subscale measures will be summarized separately during Study Period III.

Approximately 440 patients will be randomized in a 1:1 ratio between atomoxetine and placebo

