***6.2.2. Additional Secondary Objectives***

• To test the hypothesis that atomoxetine improves symptoms of ADHD compared to placebo after 12 weeks of treatment on the mean change from baseline to endpoint as measured by:

− Clinical Global Impression-ADHD-Severity (CGI-ADHD-S)

− CAARS Self Report (CAARS-S:SV)

− Patient Global Impression – Improvement (PGI-I)

• Montgomery Asberg Depression Rating Scale (MADRS): To assess the effect of atomoxetine in treating symptoms of depression in adults with ADHD as measured by the mean change in the total score after 12 weeks of treatment.

• Beck Anxiety Inventory (BAI): To assess the effect of atomoxetine in treating symptoms of anxiety in adults with ADHD as measured by the mean change in the total score after 12 weeks of treatment.

• To assess the correlation between the improvements on the AAQOL-29 Total Score with symptom reduction as measured by improvement on the CAARS- Inv:SV total ADHD symptom score.

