**12. Sample Size and Statistical Methods**

**12.1. Determination of Sample Size**

The primary objective for Study LYDZ(b) is to compare the efficacy improvement from baseline of atomoxetine dosed twice daily (BID) compared with placebo after 12 weeks in young adults using the change from baseline in the Conners’ Adult ADHD Rating Scale-Investigator Rated: Screening Version (CAARS-Inv:SV) total ADHD symptom score, the primary efficacy measure.

Approximately 440 patients will be randomized in a 1:1 ratio between atomoxetine and placebo (220 patients per group). Based on a similar ongoing trial (LYDQ) it is assumed that approximately 68% of the enrolled patients will complete the study (12 weeks of therapy). Studies LYAA & LYAO had drop-out rates of 25% & 33%, respectively, following 10 weeks of therapy.

With 220 patients per arm, assuming a 68% completion rate and the same covariance as observed in study LYCU, which includes a residual variance of 40 at week 16, and an estimated effect size of atomoxetine over placebo of 0.35, using a 5% significance level, the primary MMRM analysis is expected to have 90% power to detect a difference between atomoxetine and placebo at week 12. Two previous placebo-controlled adult ADHD atomoxetine studies (B4Z-MC-LYAA and B4Z-MC-LYAO) demonstrated

similar effect sizes on a variation of this scale, the CAARS-Inv:SV total ADHD symptom

score. The effect sizes in these two trials, based on repeated measures, were 0.35 and 0.4 (Michelson et al 2003). This sample size has been selected to achieve similar effects and allow for more than 80% power at the end of the study, assuming a 68% retention rate over 12 weeks. The sample size was estimated using the repeated measures tool

available via the Lilly Statistics website. The following table lists the required sample sizes for various effect sizes and two different drop-out rates, assuming 90% power.

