**Table LYDZ(b).2. Total N Required for Various Combinations of Effect Size and Drop-out Rate**

|  | Early Drop-out Rate | |
| --- | --- | --- |
| Effect Size | 32% | 50% |
| 0.3 | 606 | 752 |
| 0.35 | 440 | 554 |
| 0.4 | 340 | 422 |

This result is nearly identical to that obtained from the last-observation-carried-forward (LOCF) approach for a two-sided test at the 5% significance level, with an assumed standard deviation of 10.0 and 85% power to detect a difference of 3.5 points in the mean change of the CAARS-Inv:SV total ADHD symptom score. These assumptions were

based on the results from the 18-25 year old patients in LYAA & LYAO and the 18-30 year old patients in LYCU.

This sample size will also allow for an effect size of 0.325 with 80% power for the first gated secondary outcome of the AAQOL-29 total score. If the effect size increases to

0.35 or 0.40, the power will increase to 85% or 93%, respectively. The observed effect size for 18-30 year old patients in LYCU was 0.41.

The Fagerstrom Test for Nicotine Dependence, Timeline Followback: Habits, BRIEF-A, Epworth Sleepiness Scale, SASS, and PGI-I scales have never been collected in any randomized double-blind atomoxetine adult trial, so no formal power computation is possible.

These LOCF sample sizes were calculated using the "Two group t-test of equal means

(equal n’s)" module of nQuery Advisor 4.0 (1995-2000, Janet D. Elashoff).

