**Table LYDZ(b).3. Description of Secondary Efficacy Variables**

Analysis Variable Description

1. All post-baseline scores for:

a. CAARS-S:SV total ADHD symptom score and subscores

2. Change from baseline to endpoint for the following Total scores and subscores:

a. AAQOL-29

b. CAARS-S-SV

d. PGI-I

e. Habits Timeline Followback: (Alcohol, Nicotine, Caffeine, Marijuana, Drug)

f. Fagerstrom Test for Nicotine Dependence g. SASS

h. Driving Behavior Survey-S i. Driving Behavior Survey-O j. BRIEF-A

k. Epworth Sleepiness Scale l. Beck Anxiety Inventory

m. CGI-ADHD-S

n. MADRS

Post-baseline during Study Period II is defined as

Visits 3-6.

Difference between baseline and last observation on study drug (LOCF change scores). See notes on computations of total and subscores below.

3. Indicator variable for responders 3. Patients will be classified as responders according to 2 definitions:

a. 25% or greater decrease in ADHD symptoms as measured by the CAARS-Inv-SV total ADHD symptom score OR

b. Decrease on CGI-ADHD-S of 2 or more

4. Indicator variable for strong responders 3. Patients will be classified as strong responders according to the following definition:

a. 40% or greater decrease in ADHD symptoms as measured by the CAARS-Inv-SV Total

ADHD symptom score

5. Indicator variable for remitters 4. Patients will be classified as remitters according to the following definition:

a. Endpoint CGI-ADHD-S = 1 or 2

6. Indicator variable for drug compliance 5. Compliance rates will be compared across treatment groups overall and by visit.

Abbreviations: ADHD = Attention-Deficit/Hyperactivity Disorder; CAARS-Inv-SV = Conners’ Adult ADHD Rating Scale-Investigator Rated: Screening Version; CAARS-S-SV = Conners’ Adult ADHD Rating Scale-Self Rated: Screening Version; PGI-I = Patient Global Impression-Improvement; SASS

= Social Adaptation Self-Evaluation Scale; Driving Behavior Survey (Self-Report); Driving Behavior Survey (Other-Report); BRIEF-A = Behavior Rating Inventory of Executive Function-Adult Version; CGI-ADHD-S = Clinical Global Impressions-ADHD-Severity; MADRS = Montgomery-Asberg Depression Rating Scale ; LOCF = last observation carried forward.

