Variables 1-5 will be summarized for Study Period II using the last of Visits 1 and 2 as baseline and Visits 3-6 as the post-baseline visits. Variable 1a will be analyzed during Study Period II using a restricted maximum likelihood (REML)-based mixed effects model, repeated measures technique as defined for the primary efficacy analysis. This variable will be analyzed over the course of Study Period II using a contrast from the repeated measures mixed effects model at the final post baseline visit. Additionally,

visit-wise efficacy will be assessed using contrasts from this model at each post baseline

visit. This variable will be summarized separately by visit during Study Period III.

Variables 2.a through 2.n will be analyzed using a fixed-effects analysis of covariance (ANCOVA) model with terms for baseline score, treatment, and investigator. These variables will be summarized separately during Study Period III.

Variables 3-6 will be compared across treatment groups during Study Period II and separately during Study Period III using a Fisher’s Exact Test.

Time to response and time to remission will be compared across treatment groups during Study Period II using the Kaplan-Meier Product limit estimator, with the test for treatment difference being based on the log-rank test.

Correlation between the AAQOL-29 total score and the CAARS-Inv:SV total ADHD symptom score will be computed using Pearson’s correlation co-efficient to assess the relationship between these two measures.

A Fisher’s Exact Test will be used to assess baseline smoking status as a predictor of response (a 25% decrease from baseline on the CAARS-Inv:SV total ADHD symptom score) and strong response (a 40% decrease from baseline on the CAARS-Inv:SV total ADHD symptom score ) to atomoxetine treatment compared with placebo. If sparse data exists, a Chi-Squared analysis may be used instead.

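### Eleven ungated secondary scales have LOCF ANCOVA as their only score analysis despite 32% expected dropout, although the primary repeated measures model could be fitted to them

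*Protocol*

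**What the plan says.** Table LYDZ(b).3 describes the second group of secondary variables as "Difference between baseline and last observation on study drug (LOCF change scores". Section 12.2.8.1 then gives the model: "Variables 2.a through 2.n will be analyzed using a fixed-effects analysis of covariance (ANCOVA) model with terms for baseline score, treatment, and investigator".

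The group has 13 scales (the lettering runs from a to n without c). Two also have a repeated measures analysis:
- AAQOL-29, total and four subscales, in section 12.2.8.
- CAARS-S:SV, as variable 1a in section 12.2.8.1.

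For the other 11 the LOCF ANCOVA is the only analysis of the score: PGI-I, Habits Timeline Followback (TLFB), FTND, SASS, the two driving surveys, BRIEF-A, ESS, BAI, CGI-ADHD-S and MADRS.

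On dropout, section 12.1 assumes that "approximately 68% of the enrolled patients will complete the study (12 weeks of therapy". It adds that "Studies LYAA & LYAO had drop-out rates of 25% & 33%, respectively", at 10 weeks.

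On objectives, section 6.2.2 asks for MADRS and BAI change after 12 weeks. It groups CGI-ADHD-S, CAARS-S:SV and PGI-I under an effect "after 12 weeks of treatment on the mean change from baseline to endpoint". Section 6.2.3 names no time point for the remaining seven scales.

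**The concern.** With about a third of patients leaving early, an LOCF score is a week-12 value for those who stay and an earlier value for those who leave. The resulting contrast is a weighted mix of visit-specific effects, with weights set by who drops out and when. If the effect builds over time, the mix understates the 12-week effect. If both arms improve over time and one loses patients faster, the mix is shifted against that arm even when the drug does nothing. The carried value is also treated as if it had been observed at the end.

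The blinded lead-in adds to this. Sections 7.1, 9.1.1 and 9.3 allow atomoxetine to start as late as Visit 4, yet section 12.2.8.1 counts Visits 3 to 6 as post-baseline. An atomoxetine-arm patient who leaves early may therefore contribute a value recorded on placebo.

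The protocol gives no reason for treating scales differently. CGI-ADHD-S and CAARS-S:SV share an objective and are both scheduled at Visits 3 to 6, but only CAARS-S:SV gets the repeated measures contrast at the final visit.

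**Working it through.** **Inputs from the protocol.** "Approximately 440 patients will be randomized in a 1:1 ratio between atomoxetine and placebo (220 patients per group", with 68% completing, so 0.32 × 440 = 140.8, about 141 early leavers. The protocol's LOCF calculation is two-sided at 5% and was made "with an assumed standard deviation of 10.0 and 85% power to detect a difference of 3.5 points in the mean change".

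**The protocol's own LOCF figure.** Power = Φ(Δ / (SD·√(2/n)) − 1.96).
- n = 0.68 × 220 = 149.6 per arm: 3.5/1.156 − 1.96 = 1.07, power 0.857. This reproduces the stated 85%.
- n = 220 per arm: 3.5/0.953 − 1.96 = 1.71, power 0.956.

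So the stated power matches a completers-only sample, although LOCF keeps everyone with a post-baseline score. The calculation concerns CAARS-Inv:SV. For six of the 11 scales (FTND, TLFB, BRIEF-A, ESS, SASS, PGI-I) section 12.1 says no formal power computation is possible, and it gives no figures for the other five.

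**Can the repeated measures model be fitted?** Scheduled post-baseline visits in Study Period II, from the Study Schedule:

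| Scales | Visits |
|---|---|
| CGI-ADHD-S, ESS, TLFB, PGI-I | 3, 4, 5, 6 |
| MADRS, BAI, SASS, BRIEF-A, FTND, both driving surveys | 4, 6 |

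All 11 have at least two. PGI-I has no assessment at Visit 1 or 2, so neither a change from baseline nor a baseline term is available for it; the planned ANCOVA cannot be run on it as written.

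**Illustration A (assumed).** The effect is 30%, 60%, 85% and 100% of its final size at Visits 3 to 6. Dropout is spread evenly over the four intervals and is unrelated to outcome; patients with no post-baseline value are left out.
- Equal 32% dropout: (0.08×0.30 + 0.08×0.60 + 0.08×0.85 + 0.68×1)/0.92 = 0.82/0.92 = 0.89 of the Visit 6 effect.
- 40% atomoxetine versus 24% placebo, no drug effect, both arms improving by 4, 6, 7.5 and 8.5 points: atomoxetine (0.10×17.5 + 0.60×8.5)/0.90 = 7.61; placebo (0.06×17.5 + 0.76×8.5)/0.94 = 7.99; bias 7.61 − 7.99 = −0.38.
- Same split, true effect 3.5: 3.5 × (0.10×1.75 + 0.60)/0.90 = 3.01, and 3.01 − 0.38 = 2.64 after rounding.
- Error under no effect, SE = 10·√(2/205) = 0.99: 0.38/0.99 = 0.38 standard errors, so the two-sided rate is about 6.7%.

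**Illustration B (assumed).** Placebo improves by 3, 5, 7 and 8 points at weeks 2, 5, 8 and 12. The true week-12 difference is 3.5 and SD 10, with 220 per arm. Every early leaver has a value, with last observations spread evenly over Visits 3 to 5. Three effect profiles were used.

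| Share of final effect at Visits 3/4/5/6 | LOCF, equal 32% | LOCF, 40% vs 24% |
|---|---|---|
| 2/12, 5/12, 8/12, 1 | 2.85 | 2.21 |
| 0, 0.40, 0.75, 1 | 2.81 | 2.16 |
| 0, 0, 0.60, 1 | 2.60 | 1.90 |

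For the first row with equal dropout: 3.5 × (0.107×2/12 + 0.107×5/12 + 0.106×8/12 + 0.68) = 2.85. Under no effect, the unequal split gives atomoxetine 0.133×3 + 0.133×5 + 0.134×7 + 0.60×8 = 6.80 and placebo 0.08×15 + 0.76×8 = 7.28, a bias of −0.48. With SE 0.953, two-sided error is about 8%.

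**Range.** Equal dropout: 2.60/3.5 = 0.74 to 0.89 of the final effect. Unequal dropout: 1.90/3.5 = 0.54 to 2.64/3.5 = 0.75. With equal dropout and no drug effect there is no bias. Swapping the split reverses the sign of the null bias, so LOCF is not conservative by construction.

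**The case against.** Several points on the other side are sound.

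- **Objectives.** Section 6.2.3 sets no 12-week target for seven of the 11 scales. For CGI-ADHD-S and PGI-I the objective refers to endpoint, which section 12.2.1 defines as the latest non-missing observation; there LOCF is arguably the variable the protocol intends. The same objective also says 12 weeks, and CAARS-S:SV under it gets the repeated measures contrast, so the wording does not settle the matter. Only MADRS and BAI have 12-week wording without endpoint.
- **Lead-in values.** Section 12.2.1 takes baseline as the last value before active drug begins, so on that definition a lead-in value is baseline, not a carried endpoint. Section 12.2.8.1 instead takes the last of Visits 1 and 2. The two must be reconciled. The conflict also affects the repeated measures model, which does not cure it. If Visit 4 became baseline, the seven two-visit scales would have one post-baseline visit left.
- **Discontinuation visits.** Section 8.3.1 has early leavers complete end-of-study procedures, so the carried value usually comes from the week of leaving. It is still not a week-12 value.
- **Magnitudes.** They borrow the CAARS-Inv:SV difference and SD, assume a four-visit profile, and make dropout unrelated to outcome, a setting that favours the repeated measures model.

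A reader might infer that nearly all secondary evidence rests on LOCF. It does not: the gated AAQOL-29 tests and CAARS-S:SV have the repeated measures model, and the responder, remission and time-to-event variables use Fisher's exact or log-rank tests.

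A reader might also infer that LOCF in section 12.2.7 should be replaced because it does not probe the missing-at-random assumption of the primary analysis. The document does not support that: LOCF there only accompanies a repeated measures primary, and further sensitivity analyses are commonly left to the SAP, which is not shown.

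**Conclusion.** The point holds for 11 scales outside the gated testing sequence. Their only named score analysis carries the last value forward with 32% dropout expected, while a model already specified in the protocol could be fitted to each. It is strongest for MADRS and BAI, whose objectives ask for change after 12 weeks, and for CGI-ADHD-S, which is handled differently from CAARS-S:SV on the same schedule and under the same objective. It is weaker for the seven functional scales, which have no stated time point, and the gain is limited for the seven scales measured only at Visits 4 and 6 (the two groups overlap but are not the same).

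The bias cannot be sized from the protocol. Under the assumptions shown, LOCF keeps 74% to 89% of the final-visit effect with equal dropout and 54% to 75% with a 40% versus 24% split; in the latter case two-sided error under no effect is about 7% to 8%. The lead-in concern holds only on the baseline definition in section 12.2.8.1. The primary analysis, the gated tests and the CAARS-S:SV repeated measures analysis are untouched.

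**What to change.** In section 12.2.8.1, make the section 12.2.6 repeated measures model, with the Visit 6 contrast, the main analysis for every ungated scale with at least two scheduled post-baseline visits in Study Period II:
- CGI-ADHD-S, ESS, TLFB and PGI-I at Visits 3 to 6, with PGI-I fitted without baseline terms.
- MADRS, BAI, SASS, BRIEF-A, FTND and both driving surveys at Visits 4 and 6.

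State how early-discontinuation assessments are assigned to visits, and keep LOCF ANCOVA as a supplementary table. Leave section 12.2.7 as it is. Reconcile the baseline definitions in sections 12.2.1 and 12.2.8.1, which matters whichever model is used.

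No new data are needed. Section 12.2.1 allows changes that do not alter a principal feature to be documented in the SAP before unblinding without an amendment, so the cost is SAP text and programming. The downside is less direct comparability with earlier LOCF results, which the supplementary table covers.

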**9.3. Method of Assignment to Treatment**

Patients who meet all criteria for enrollment will be randomized 1:1 to double-blind treatment sometime between Visit 2 and Visit 4. However, because of the potential for a double-blind placebo lead-in and because any patients randomly assigned to atomoxetine may receive placebo some time during the potential lead-in phase, patients in the atomoxetine group may receive atomoxetine as early as Visit 2 or as late as Visit 4. During the double-blind treatment period of the study (Study Period II) assignment to treatment groups will be determined by a computer-generated random sequence using an interactive voice response system (IVRS). The IVRS will be used to assign packages containing double-blind study drug to each patient.

During the open-label extension period of the study (Study Period III) market-image atomoxetine will be supplied by Lilly.

To achieve between group comparability for site factors, patients will be randomized at the site level.

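### Responder and remitter rates are compared with an unadjusted Fisher's exact test, which is valid but gives up a few points of power that the baseline scores already collected could recover

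*Protocol*

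**What the plan says.** Section 12.2.8.1 fixes the method for the binary efficacy variables: "Variables 3-6 will be compared across treatment groups during Study Period II", and separately in Study Period III, with a Fisher's exact test. Table LYDZ(b).3 defines them as follows:

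- Variable 3, responder: a fall of at least 25% in CAARS-Inv:SV total or, as a second definition, a fall of at least 2 points in CGI-ADHD-S.
- Variable 4, strong responder: a fall of at least 40% in CAARS-Inv:SV total.
- Variable 5, remitter: endpoint CGI-ADHD-S of 1 or 2.
- Variable 6: drug compliance.

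The continuous secondary variables in the same section get a "fixed-effects analysis of covariance (ANCOVA) model with terms for baseline score, treatment, and investigator". The primary MMRM (Section 12.2.6) and its LOCF ANCOVA (Section 12.2.7) also carry baseline and investigator. Section 9.3 says: "To achieve between group comparability for site factors, patients will be randomized at the site level". Section 12.2.1.1 gives a rule for pooling small sites that applies to all analyses. The study schedule (Attachment LYDZ(b).1) records CAARS-Inv:SV and CGI-ADHD-S at Visits 1 and 2.

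**The concern.** The binary efficacy variables are dichotomised from scores that the protocol elsewhere analyses with baseline and investigator in the model, yet their own test uses neither. No reason is given. Two things can cost power. Fisher's exact test runs below its nominal 5% level, and leaving out a prognostic covariate dilutes the treatment contrast.

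Remission is the clearest case. Entry requires CGI-ADHD-S of at least 4 (Section 8.1, criterion 3). A patient entering at 4 must fall 4 − 2 = 2 points to remit, and one entering at 6 must fall 6 − 2 = 4. Baseline severity therefore bears directly on the outcome. For the 25% and 40% CAARS definitions baseline is already the denominator, so it is uncertain how much further adjustment would help.

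At stake is efficiency on ungated secondary variables, together with an effect estimate that takes account of baseline.

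**Working it through.** **What the plan gives.** It states no response or remission rate, power, site variance or prognostic strength for variables 3-5. The nearest figure is the LOCF sizing in Section 12.1: difference 3.5, SD 10, 85% power. With 220 × 0.68 = 149.6, about 150 per arm, power = Φ(3.5/(10√(2/150)) − 1.96) = Φ(3.03 − 1.96) = 85.8%. The figure reproduces. It does not bear on the binary tests, but it shows that Section 12.1 counts about 150 completers per arm. Endpoint is the last post-baseline observation (Section 12.2.1), so the number analysed should lie between 150 and 220.

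**Step 1: Fisher's conservatism, by enumerating every table.** Fisher's two-sided p-value sums the hypergeometric probabilities of tables no more likely than the one observed. The chi-square rejects when (|x − y|/n)/√(P(1 − P)·2/n) > 1.96, with P = (x + y)/2n. Size or power is Σ Bin(x; n, p₁)·Bin(y; n, p₀) over rejected tables. The rates are assumed.

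| n per arm | Rates | Fisher | Chi-square |
|---|---|---|---|
| 220 | 30% v 43% | 78.7% | 81.4% |
| 220 | 40% v 55% | 86.7% | 88.6% |
| 220 | 10% v 20% | 81.1% | 84.5% |
| 150 | 30% v 43% | 60.3% | 64.7% |
| 150 | 10% v 20% | 62.9% | 68.6% |

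The loss is 1.9 to 3.4 points at 220 per arm and 4.4 to 5.7 at 150. With equal rates of 10-50% and 220 per arm, Fisher's true size is 3.5-4.0%.

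**Step 2: adding baseline and site, by simulation.** The set-up is 440 patients in 35 sites, with allocation balanced within site. Logit(response) = α + λ·treatment + site effect (SD σ) + β·standardised baseline. All of these values are assumptions.

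| Setting (runs) | Fisher | Chi-square | CMH by site | Baseline only | Baseline and site |
|---|---|---|---|---|---|
| Control 35%, λ 0.6, σ 0, β 0 (4,000) | 84.9 | 86.9 | – | – | 86.7 |
| Same, σ 0.5, β 0.3 (4,000) | 81.6 | 83.3 | – | – | 84.8 |
| Same, σ 0.8, β 0.5 (4,000) | 74.1 | 76.2 | – | – | 81.6 |
| 43% v 56%, OR 1.65 per SD (3,000) | 75 | – | 78 | 79 | – |
| Same rates, modest strength, σ 0.35 (1,500) | 74.1 | 76.6 | 76.9 | 78.7 | – |
| Modest strength (500) | 76 | 78 | 78 | 81 | 82 |
| 44% v 56%, OR 2.5 per SD (3,000) | 73 | – | 75 | 82 | – |
| Same rates, strong, σ 0.35 (1,500) | 70.1 | 72.2 | 72.7 | 79.8 | – |
| Remission 27% v 38%, OR 2.5 per SD (3,000) | 66 | – | 69 | 74 | – |

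The control rate of 35% is that at an average site and baseline. The last column is a linear model in the 4,000-run rows and a site-conditional logistic model in the 500-run row. Monte Carlo error is about 1 point, or √(0.8 × 0.2/500) = 1.8 points for 500 runs.

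- *Moderate strength, total loss:* 84.8 − 81.6 = 3.2; 79 − 75 = 4; 78.7 − 74.1 = 4.6; 81 − 76 = 5 (6 with site, in the smallest set).
- *Strong, total loss:* 81.6 − 74.1 = 7.5; 74 − 66 = 8; 82 − 73 = 9; 79.8 − 70.1 = 9.7 in one set.
- *Part due to site (CMH minus chi-square):* 0.3 and 0.5 points at σ 0.35. In a further 2,000-run set it was 85.0 − 83.9 = 1.1 at σ 0.5 and 78.5 − 75.1 = 3.4 at σ 0.8.
- *Part due to baseline (logistic minus chi-square):* 78.7 − 76.6 = 2.1 at modest strength and 79.8 − 72.2 = 7.6 at strong.
- *No prognostic effect:* adjustment adds nothing over the chi-square (86.7 v 86.9).

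**Step 3: size under the null.** In the 3,000- and 4,000-run sets Fisher's size was 3.3-4.5% and that of the adjusted tests 4.3-5.3% at 440 patients. Fisher fell to 2.6% in an extreme setting (σ 1.0, β 0.7). The linear model reached 5.7% with only 300 patients over 35 sites, and CMH 5.8% in one 2,000-run setting (σ 0.8), so thin sites need care.

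**The case against.** Fisher's test is valid and is the protocol's usual choice for categorical comparisons. Its size is guaranteed at or below 5% without a model or large-sample approximation, and it copes with sparse cells. The gated objectives are all AAQOL-29 (Section 6.2.1), and no power is claimed for the binary variables. Adjusted analyses of the underlying CAARS and CGI-ADHD-S scores are already planned. Section 12.2.1 lets a change of this kind go into the SAP, which was not available and may already contain it. Every magnitude above is assumed. All of this stands, and it limits the point to efficiency. It does not remove the loss, because the protocol states a specific test rather than leaving the choice open.

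A reader might infer several stronger things that the documents do not support:

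- *That ignoring the randomisation factor makes the test invalid or inflates false positives.* The error runs the other way.
- *That Fisher brings no benefit.* It brings guaranteed size, though that is worth little at 220 per arm and mid-range rates.
- *That baseline is a strong predictor.* The protocol gives no evidence of this, and entry at CGI-ADHD-S of 4 or more narrows the baseline range on a 7-point scale.
- *That site is the main source of loss.* At σ 0.35 it accounts for under 1 point.

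**Conclusion.** The point holds as a modest loss of efficiency. At 220 per arm Fisher's test gives up about 2-3 points of power to an unadjusted chi-square. Against a baseline-adjusted analysis it gives up about 3-5 points in all at moderate prognostic strength and about 7-9 at strong. Most of the recoverable power comes from dropping Fisher and adding baseline, and site matters only if it is strongly prognostic. These sizes depend on assumed response rates and on assumed site and baseline effects. If neither site nor baseline is prognostic, only the 2-3 points remain. The argument is firm for remission and uncertain for the percentage-decrease CAARS definitions. The primary analysis and the gated sequence are untouched.

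**What to change.** For variables 3-5 in Study Period II, replace Fisher's exact test with logistic regression on treatment and the relevant baseline score: CAARS-Inv:SV total for the percentage definitions, CGI-ADHD-S for the 2-point fall and for remission. Condition on (stratify by) pooled investigator rather than fitting a term for each site, so that sparse site terms do not bias the estimate. A CMH test stratified by pooled investigator is the simpler alternative, but it leaves out baseline. Report a risk difference or odds ratio with 95% CI. Keep Fisher as a sensitivity analysis and for sparse tables. Compliance (variable 6) can stay with Fisher.

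The cost is a sentence of text and a few lines of code. Section 12.2.1 allows it to be recorded in the SAP before unblinding, without an amendment, provided it is not a principal feature. The price is reliance on a model or large-sample approximation, and an odds ratio that is conditional on baseline unless a marginal risk difference is reported.
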